### Statistical analysis

Analyses will be made using SAS statistical software (version 9.3) by a statistician in Peking University Clinical Research Institute. Data will be analyzed according to the “intent-to-treat” principle. A two-sided significance level of 5% will be used for all analyses.

Descriptive statistics will be used to summarize demographic and clinical characteristics of participants randomised to the intervention and control groups. The difference between two groups on demographic characteristics, socioeconomic status, clinical characteristics and follow-up retention rate will compared using t-tests (or Wilcoxon rank sum test) and chi-square test/Fisher’s exact test as appropriate.

Primary outcome (improvement rate of urination function in 1 year) analyses will be carried out by Cochran-Mantel-Haenszel tests taking into center effect.

The difference in urodynamic parameter, anorectal function and pelvic function between intervention and control groups will be determined using t-tests or Wilcoxon rank sum tests as appropriate. The severity of urinary incontinence will be analyzed using the Wilcoxon rank sum test. The differences in QOL (evaluated by EQ-5D, PISQ-12, PFDI-20 and ICIQ/OABss) between intervention and control group will be determined using repeated measure analysis of variance (ANOVA). DFS and OS survival curves will be calculated using the Kaplan-Meier method, and compared using the log-rank test. Cox proportional hazards models will also be used to calculate hazard ratio and 95% confidence interval, with other risk factors (such as cancer stage and tumor localization) as covariates.

The incidence of adverse events between 2 groups will be compared with the chi-square test/Fisher’s exact test. Descriptive statistics will be used to summarize incidence rates of adverse events and serious adverse events.

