## Background

Cervical cancer is one of the most commonly diagnosed malignant tumors among women all over the world [1]. There are an estimated 131.5 thousand newly diagnosed cervical cancer cases per year in China, accounting for 28.8% of the world’s cases. In all, 30% of cervical cancer patients are younger than 30 years [2]. With the widespread availability of cervical cancer screening, the proportion of early stage cervical cancer is increasing year by year. The standard treatment for patients with early stage cervical cancer is class III radical hysterectomy plus pelvic lymphadenectomy, with chemotherapy and/or radiotherapy supplemented as needed. The 5 year survival rate after treatment can reach as high as 90% [2]. Pelvic vessels, autonomic nerve fibers and ligaments could be affected by the resection of anterior, lateral and posterior parametrium and vaginal cuff. The unintended interruption may result in pelvic floor dysfunction including disorders of lower urinary tract, defecation disorders and sexual dysfunction. Though the cancer could be cured by the surgery, many patients may suffer from decreased quality of life due to the poor pelvic function following radical hysterectomy.

It has been reported that 70%–85% cervical cancer patients suffer from bladder dysfunction following radical hysterectomy [3, 4]. The main symptom of short-term bladder dysfunction is urinary retention (UR) while the long-term postoperative bladder disorder is urinary incontinence [5, 6]. Usually the time of indwelling urinary catheter after class III radical hysterectomy is 2 weeks, but it lasts up to 1 month in about 15% patients and even more than half a year in 3% patients because of chronic urinary retention [6, 7].

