### Randomisation and blinding

Central randomisation via interactive web response system will be carried out by Peking University Clinical Research Institute, which is independent of the trial administration office. The allocation sequence is computer-generated 1:1 with dynamic randomisation system using minimization. Randomisation is conducted with varying block size and will be stratified by menopausal status (menopause vs. non-menopause) and surgical modality (laparoscopic radical hysterectomy or abdominal radical hysterectomy). Intervention assignment cannot be blinded for the participants and investigators due to device stimulation and blank control.

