### Initial screening, assessment and follow-up

After providing informed consent, participants are asked standardized questions about their demographic characteristics, socioeconomic status and medical history. Clinical data is extracted from the medical records regarding primary tumor, time of primary diagnosis, surgical operation, physical examination, laboratory testing, gynecological examination and imaging examination (Table 1).

**Table 1 Tab1:** Baseline screening, assessment, and follow-up schedule

	At baseline	Time after surgery								Early withdrawal
		14 days	21 days	28 days	3 months	6 months	12 months	18 months	24 months	
Follow-up time window (days)		±2	±2	±2	±7	±7	±7	±7	±7	
Informed consent	●									
Demographic characteristics	●									
Socioeconomic status	●									
Medical history	●									
Information on tumor clinical evaluation and surgical operation	●									
Physical examination	●									
Blood routine examination	●				●	●	●	●	●	
Blood clotting function	●									
Routine urine test	●				●	●	●	●	●	
Routine stool test	●				●	●	●	●	●	
Blood biochemistry	●				●	●	●	●	●	
Hormone testing^a^	●				●	●	●	●	●	●
Tumor biomarkers^b^	●				●	●	●	●	●	●
Gynecological examination^c^	●				●	●	●	●	●	●
Abdominal/pelvic CT/MRI	●	▲								
Chess X-ray	●					●	●	●	●	●
Randomization	●									
Assessment of residual urine^d^		●	●	●	●	●	●			
Uroflowmetry				●	●					
Urodynamic tests				●						
Anorectal function evaluation				●						
Pelvic floor functional testing				●	●					
EQ-5D^e^					●	●	●		●	
PISQ-12^f^						●	●		●	
PFDI-20^g^					●	●	●		●	
ICIQ/OABss^h^					●	●	●		●	
Adverse events	●				●	●	●	●	●	●

●: Indicates mandatory items

▲: Investigator will decide whether to perform the testi according to clinical signs or clinical evaluation

^a^Hormone testing includes estradiol, progesterone, testosterone, prolactin, follotropin and luteinizing hormone

^b^Tumor biomarkers includes squamous cell carcinoma antigen, CA125, CA199 and carcinoembryonic antigen

^c^Gynecological examination includes Human Papillomavirus and Thinprep Cytological Testing

^d^Residual urine is evaluated by B ultrasound

^e^EQ-5D: European Quality of Life-5 Dimensions

^f^PISQ-12: Prolapse/Urinary Incontinence Sexual Questionnaire short form

^g^PFDI-20: Pelvic Floor Distress Inventory

^h^ICIQ/OABss: International Consultation on Incontinence Questionnaire/Overactive Bladder Symptom Score

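### Baseline characteristics are significance-tested between randomised arms, while the primary CMH test names only centre and omits the allocation factors, at a modest cost in precision

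*Protocol article*

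**What the plan says.** The Statistical analysis section of the protocol article first promises a description: "Descriptive statistics will be used to summarize demographic and clinical characteristics of participants randomised to the intervention and control groups". It then adds hypothesis tests: "The difference between two groups on demographic characteristics, socioeconomic status, clinical characteristics and follow-up retention rate will compared using t-tests", with Wilcoxon, chi-square or Fisher tests where suitable. The general rule of that section applies to them too: "A two-sided significance level of 5% will be used for all analyses".

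For the primary outcome, "analyses will be carried out by Cochran-Mantel-Haenszel tests taking into center effect". No other factor is named. Covariates appear only for disease-free and overall survival, in Cox models "with other risk factors (such as cancer stage and tumor localization) as covariates".

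Under Randomisation and blinding, allocation "will be stratified by menopausal status (menopause vs. non-menopause) and surgical modality (laparoscopic radical hysterectomy or abdominal radical hysterectomy"). Centre is not named there. Table 1 schedules demographic characteristics, socioeconomic status, medical history and "Information on tumor clinical evaluation and surgical operation" at baseline.

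**The concern.** Two uses of the baseline data look the wrong way round.

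First, allocation is central and computer-generated, so any difference in a baseline characteristic is due to chance. A significant p-value reports only that chance. A non-significant one does not show that an imbalance in a strong predictor is harmless. Some flags are to be expected, and in an unblinded trial they invite after-the-fact adjustment or unfounded doubt about the randomisation.

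Second, the endpoint that sizes the trial gets less adjustment than the survival endpoints. The two factors judged important enough to steer allocation are absent from its analysis, and the one factor present is not named in the allocation. What is at stake is precision: a covariate that predicts recovery of urination would raise power if it were modelled, and no new patients would be needed.

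**Working it through.** **The plan's own figure.** Inputs from Sample size consideration: 70% vs 50%, two-sided 5%, 80% power, 10% drop-out, 1:1.

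n per arm = [1.960 × √(2 × 0.6 × 0.4) + 0.842 × √(0.7 × 0.3 + 0.5 × 0.5)]² / 0.2² = 93. Then 93 / 0.9 = 103.3, rounded up to 104 per arm, or 208 in total. The stated size is reproduced (no continuity correction).

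**Baseline tests.** The article does not give the number of variables, so 10 to 30 is assumed, with independence. P(at least one p < 0.05) = 1 − 0.95^k.

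| k tests | expected false flags (0.05k) | P(at least one) |
|---|---|---|
| 10 | 0.5 | 40% |
| 20 | 1.0 | 64% |
| 30 | 1.5 | 79% |

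**Retention.** This is a post-randomisation outcome, so the argument above does not cover it. Whether a test is informative is a separate question. Take 6% vs 14% lost as an assumed example, with 104 per arm and a pooled rate of 10%. Then z = [0.08 − 1.960 × √(2 × 0.1 × 0.9 / 104)] / √[(0.06 × 0.94 + 0.14 × 0.86) / 104] = (0.080 − 0.0815) / 0.0412 ≈ −0.04, so power is about 49%. A non-significant result would say little; an interval would say more.

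**Adding one binary factor to the CMH test.** Simulation with 8,000 trials per scenario, 94 per arm, nine equal centres with no centre effect, factor prevalence 50%, and 70% vs 50% overall. The prognostic odds ratio is assumed, because the article gives none.

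| Prognostic odds ratio | CMH by centre | CMH by centre × factor (18 strata) | CMH by factor only |
|---|---|---|---|
| 1 | 79% | 77% | 80% |
| 2 | 79% | 78% | 81% |
| 3 | 79–80% | 80% | 83% |
| 5 | 79–80% | 82% | 85% |

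Type I error of the centre-only test was about 5% throughout, with one exception. With a factor of odds ratio 5 balanced exactly by design it was about 3.5%, which is conservative.

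**Adding one score to a model, centre kept in both analyses.** The score is continuous, with assumed log-odds per standard deviation.

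| Log-odds per SD (odds ratio) | adjusted power | centre only |
|---|---|---|
| 0 (1.0) | 78% | 77% |
| 0.5 (1.65) | 81% | 79% |
| 0.8 (2.2) | 85% | 79% |

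The one-point gap in the first row cannot be real, since that covariate carries no information, so it counts as zero. The gain is therefore about 0 to 6 points.

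**Why not more CMH strata.** Centre × menopausal status × modality gives 9 × 2 × 2 = 36 strata, and 208 / 36 ≈ 6 patients per stratum. The binary-factor table shows that finer stratification can lose about 2 points when the factor predicts nothing.

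**The case against.** A centre-stratified CMH test is valid. Chance imbalance is already covered by the 5% error rate, and menopausal status and modality are controlled through the allocation. Further covariates may stand in an analysis plan that is not shown. The article does not link age or stage to bladder recovery. Descriptive summaries are planned as well, and no stated rule lets a baseline p-value change the primary result.

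Most of this stands. It limits the point to wording and precision. It does not rescue the baseline tests, which the article plans outright. Nor does control through allocation make adjustment idle: when a prognostic factor is balanced by design and then ignored, the test becomes conservative. How far age predicts recovery is an assumption, and this is why the gain is given as a range that starts at zero.

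A reader might also infer that the protocol collects, and then ignores, the very cause of bladder damage that it names. The text does not support this. The Background says that vessels, nerves and ligaments "could be affected by the resection of anterior, lateral and posterior parametrium and vaginal cuff". That is the resection itself, not its extent. Every participant must have class III surgery, and nerve-sparing surgery is excluded. The baseline schedule lists surgical information only in general terms and names no variable for extent of resection.

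**Conclusion.** The point holds as a matter of analysis choice and is modest in size. The baseline tests cannot inform under sound randomisation; deleting them improves presentation and changes no result. The primary analysis omits the two allocation factors and other baseline values that could sharpen it. The cost is about 0 to 6 points of power, conditional on assumed prognostic odds ratios of 1.0 to 2.2 per SD for a score built from the covariates.

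A reader might conclude that the omission biases the estimated TENS effect or makes false positives more likely. Neither follows: the randomised comparison stays unbiased and type I error is at or below about 5%. Comparing retention between arms in an unblinded trial is also legitimate. Only reliance on a p-value for it is weak.

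**What to change.** In the Statistical analysis section:

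- Show baseline characteristics by arm descriptively, without p-values. Report retention by arm with reasons for loss and a 95% confidence interval for the difference.
- Prespecify a model-based primary analysis, for example logistic regression giving a standardised difference in improvement rate with 95% confidence interval, adjusted for centre, menopausal status, surgical modality and age. FIGO stage is optional. Keep the centre-stratified CMH test and the unadjusted rates as support.
- Do not cross-classify all factors in the CMH test.
- Leave out extent of resection unless it is shown to be recorded.

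The cost is a change of wording and one more model, with covariates fixed before outcome data by arm are seen. The listed covariates need no new visits or data, and the sample size stays at 208.

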### Study endpoints

The primary endpoint is improvement rate of urination function. Based on self-urination status and residual urine evaluated by B ultrasound following catheter removal and self-urination, efficacy is classified into three levels: 1) recovery: automatic micturition is achieved by patients with residual urine ≤50 ml; 2) improvement: automatic micturition is achieved by patients with residual urine 50–100 ml; 3) invalid: automatic micturition is not achieved, or automatic micturition is achieved but with residual urine ≥100 ml. Improvement rate is calculated as follows: (the number of recovery participants + the number of improvement participants)/the total number of enrolled participants *100%.

Secondary endpoints are: (1) urodynamic parameter, including maximal uroflowmetry, micturition curve, bladder sensation, detrusor muscle stability, detrusor muscle function of contraction, stress urinary incontinence, urinary retention and lower urinary tract obstruction; (2) urinary incontinence evaluated by 1 h pad test is defined as follows: <1 g continence, 1–10 g mild incontinence, 11-30 g moderate incontinence, 31-50 g severe incontinence, >50 g extremely severe incontinence; (3) anorectal function, including rectal sensation, rectal maximum volume, reflex of rectal anal internal sphincter, reflex of rectal anal external sphincter and balloon expulsion testing; (4) pelvic function, including muscle strength of type I and type II muscle fiber of pelvic muscle, fatigue of pelvic muscle, vaginal dynamic pressure and neural reflex; (5) QOL evaluated by EQ-5D, PISQ-12, PFDI-20 and ICIQ/OABss; (6) overall survival (OS), calculated as the time from initial diagnosis to death from any cause or the date of last follow-up for surviving subjects; (7) disease-free survival (DFS), defined as the period from the date of initial diagnosis to the date of recurrence, metastasis, death due to any cause or the date of last follow-up for surviving subjects; (8) adverse events.

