### Sample size consideration

We expect improvement rate of urination function 70% in the intervention group and 50% in the control group. Based on a difference of 20% between groups on the primary outcome, assuming 10% drop-out rate, a total of 208 participants (at 1:1 ratio, 104 subjects in each group) are required to provide 80% power, with the use of two-sided significance level of 0.05.

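### The primary outcome is analysed at 1 year, but the planned 50% control rate does not fit 1 year on the protocol's own background figures, so the stated 80% power does not apply to that analysis

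*Protocol article*

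**What the plan says.** Under Study endpoints, "The primary endpoint is improvement rate of urination function". Success is spontaneous voiding with residual urine in the two better bands, up to 100 ml. Failure is no spontaneous voiding, or residual urine of 100 ml or more. The denominator is everyone enrolled. No visit is named there or in the Abstract.

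The Sample size consideration gives "We expect improvement rate of urination function 70% in the intervention group and 50% in the control group", also undated, and concludes that "a total of 208 participants (at 1:1 ratio, 104 subjects in each group) are required to provide 80% power", after 10% drop-out and "with the use of two-sided significance level of 0.05".

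A time appears only under Statistical analysis, in the words "Primary outcome (improvement rate of urination function in 1 year"; the test named there is Cochran-Mantel-Haenszel, allowing for centre.

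Residual urine is measured at six visits: days 14, 21 and 28 and months 3, 6 and 12 (Initial screening, assessment and follow-up, and Table 1).

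On the natural course, the Background says that after this operation the catheter usually stays 2 weeks, but "it lasts up to 1 month in about 15% patients and even more than half a year in 3% patients". The Intervention section removes the catheter at days 14, 21 or 28 once residual urine is under 100 ml, almost the same threshold as the endpoint.

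**The concern.** The planning rates and the analysis time describe different stages of recovery. A 50% control success rate implies that half of usual-care patients still fail. The Background describes a condition that has largely resolved long before 12 months, and it presents retention as the short-term disorder. TENS itself is given from about day 7 for two to three weeks.

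If the primary test is run as written, both arms are likely to be near the ceiling. The trial could then report no effect even if TENS speeds early recovery, which is the question it sets out to answer. If the team noticed this only after seeing data and moved to an earlier visit, that would be a data-driven choice among the remaining visits, and the nominal 5% error rate would no longer hold.

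**Working it through.** **1. Reproduce the stated sample size.** Inputs from the Sample size consideration: 50% vs 70%, two-sided 0.05, power 80%, drop-out 10%. With pooled variance and no continuity correction:

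n = [1.960·√(2·0.6·0.4) + 0.842·√(0.5·0.5 + 0.7·0.3)]² / 0.20² = 93 per arm.

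93 / 0.90 = 103.3, rounded up to 104 per arm, 208 in total. This matches, so the arithmetic is sound. The question is whether the rates belong to 1 year.

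**2. Control rate at 1 year.** Assumption: being catheterised approximates failure. With 3% catheterised beyond half a year, control success at 1 year is about 100 − 3 = 97%. Some catheter-free patients may still have 100 ml or more, so I also use 90% as a deliberately lower value. The 90% is an assumption and is not in the documents. The largest possible gain is then 3 to 10 points. A gain of 20 points is impossible at any control rate above 80%.

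**3. Carry the planned effect over.** The documents do not say on which scale the effect is constant, so two are used:
- odds ratio = (0.7/0.3)/(0.5/0.5) = 2.33;
- failure ratio = 0.30/0.50 = 0.6.

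At 97%: the odds become (0.97/0.03)·2.33 = 75.4, giving 98.7%; the failure ratio gives 1 − 0.03·0.6 = 98.2%. At 90%: the odds become 9·2.33 = 21, giving 95.5%; the failure ratio gives 1 − 0.10·0.6 = 94.0%.

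**4. Power.** Exact binomial enumeration of the uncorrected two-sided chi-square test, at 93 (evaluable) and 104 (randomised) per arm. This ignores stratification by centre.

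| Control | TENS | Basis | Power, n = 93 | Power, n = 104 |
|---|---|---|---|---|
| 50% | 70% | as planned | 80% | 85% |
| 97% | 98.7% | odds ratio 2.33 | 10% | 11% |
| 97% | 98.2% | failure ratio 0.6 | 7% | 8% |
| 97% | 100% | best possible | 31% | 38% |
| 90% | 95.5% | odds ratio 2.33 | 30% | 33% |
| 90% | 94.0% | failure ratio 0.6 | 17% | 19% |

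**5. All-enrolled denominator.** If the 10% drop-outs count as failures in both arms (104 per arm), 97% becomes 0.97·0.9 = 87.3%. The TENS rates of 98.2%, 98.7% and 100% become 88.4%, 88.8% and 90.0%. Exact power is 6%, 6% and 10%.

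**6. Earlier visits.** On the same proxy, the share still catheterised after 2 weeks is 15% (if the 3% is part of the 15%) or 15 + 3 = 18% (if separate). Control success would then be about 82-85%, not 50%. At 82%, power is 48-53% with the odds ratio (82% vs 91.4%) and 29-32% with the failure ratio (82% vs 89.2%).

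**The case against.** Several points against this deserve weight.

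- **Catheter time is not residual urine.** Removal is tied to the 100 ml threshold only up to day 28. After that its timing follows the patient's recovery, and a catheter-free patient with 100 ml or more still counts as a failure. The 3% also comes from cited work that cannot be checked here. This stands, and it is why 97% is an upper guide and a range is shown. It does not rescue the plan: at 90% the planned effect still gives at most 33% power.
- **The Background also reports bladder dysfunction in 70-85%.** That figure is undated and covers more than retention, so it does not support 50% failure at 1 year.
- **The phrase may mean within 1 year, not at 1 year.** A cumulative reading can only raise control success, so the ceiling is worse.
- **The phrase is a parenthesis in a condensed article, and a fuller document may name the visit.** That is possible. However, the article does state a time, and that time conflicts with its own figures, so this is more than an omission.

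A reader might go further and infer that day 21 or day 28 is the right visit. The documents do not support that. Step 6 puts control success after 2 weeks at about 82-85%. In addition, patients with more than 100 ml at day 14 receive a further 7 days of treatment, so their course is not finished at day 21. Day 14 may sit nearer to 50%, but treatment is then only about half given. Nothing in the text ties 50% to any visit.

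**Conclusion.** The point holds as an inconsistency between the analysis time and the planning rates. The 208 is correct for 50% vs 70%, but those rates are not credible at 1 year on the protocol's own background. With the planned relative effect, power at 1 year is about 7-11% at a 97% control rate and 17-33% at 90%. It is about 6-10% if drop-outs count as failures at the 97% rate, where the upper end already assumes that every TENS patient who stays in the trial succeeds.

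These sizes rest on catheterisation as a proxy for failure, on an assumed lower value of 90%, and on the two effect scales. Two stronger readings should be avoided. One is that the control rate will be 97%: it is a proxy, and it does not use the all-enrolled denominator. The other is that the test could detect nothing. Even at a 97% control rate, perfect success on TENS would give 31-38% power, and at lower control rates an effect larger than the planned relative one could be detected.

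**What to change.** Replace the 1-year wording with one pre-specified early postoperative visit, stated identically in the Abstract, Study endpoints, Sample size consideration and Statistical analysis. It should be the existing visit for which the 50% control rate was estimated. The sponsor should confirm it before any outcome data are seen and justify the 50% and 70% for that visit. The other residual-urine visits, including 12 months, become secondary.

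If 1 year is what the sponsor intends, restate the Sample size consideration with a justified 1-year control rate on the all-enrolled denominator, and give the power that results.

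Cost: the first option changes wording only, since all six visits and measurements already exist. Its price is that the 1-year result becomes a secondary claim. If the 50% cannot be justified for any visit, the sample size would have to be worked out again. The second option would, on the figures above, mean accepting low power or a much larger trial: about 2,550 per arm for 97% vs 98.2%.

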## Methods and design

### Trial design and setting

The trial is conducted as a clinical, multicentre, randomised controlled trial with balanced randomisation (1:1) to examine the efficacy of transcutaneous electrical stimulation (TENS) treatment on the recovery of urinary function among postoperative patients with early cervical cancer. After class III radical hysterectomy, participants with early cervical cancer (International Federation of Gynecology and Obstetrics [FIGO], stage Ia2, Ib1 and IIA1) will be randomly assigned to an intervention or control group. Participants will be stratified by menopausal status and surgical modality. Subjects will be recruited continuously by oncologists from gynecology departments in nine hospitals of Beijing city: Peking University People’s Hospital; Peking University First Hospital; Peking University Third Hospital; Cancer Institute and Hospital, Chinese Academy of Medical Sciences; Peking University Cancer Hospital & Institute; The General Hospital of the People’s Liberation Army; Beijing Obstetrics and Gynecology Hospital, Capital Medical University; Beijing Chaoyang Hospital, Capital Medical University; and Beijing Hospital. Figure 1 illustrates the flow diagram of the study for both the intervention and control groups.

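### The primary test names centre only and omits the two factors used to balance allocation; if those factors are prognostic, it is mildly conservative and gives up a few points of power

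*Protocol article*

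**What the plan says.** **Primary test.** The Statistical analysis section of the protocol article states that primary outcome "analyses will be carried out by Cochran-Mantel-Haenszel tests taking into center effect". The Abstract says the same. Neither place names another stratification factor or covariate for this test.

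**Allocation factors.** Trial design and setting says: "Participants will be stratified by menopausal status and surgical modality". Randomisation and blinding and the Abstract name the same two factors. None of the three lists centre, although patients come from "oncologists from gynecology departments in nine hospitals of Beijing city".

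**Allocation method.** Randomisation and blinding describes allocation "with dynamic randomisation system using minimization. Randomisation is conducted with varying block size". These are two different procedures given for one sequence.

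**Sizing.** "We expect improvement rate of urination function 70% in the intervention group and 50% in the control group". With 10% drop-out, 80% power and two-sided 0.05, the total is 208, or 104 per arm.

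**The concern.** Balancing allocation on a prognostic factor removes that factor's contribution to the chance difference between arms. A test that ignores the factor still counts this contribution in its variance. Its standard error is then too large, its true type I error falls below the nominal 5%, and some of the precision that the balancing bought is not used.

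Here the factors built into allocation are absent from the primary test, and the factor in the test is absent from allocation. At stake is efficiency in a trial sized at 80% power with no stated reserve. A false claim of benefit is not at stake.

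**Working it through.** **1. The planned figure.** Inputs from Sample size consideration: 0.70 and 0.50 (mean 0.60), two-sided 0.05, 80% power, 10% drop-out.

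n per arm = [1.960·√(2·0.60·0.40) + 0.842·√(0.70·0.30 + 0.50·0.50)]² / 0.20² = [1.358 + 0.571]² / 0.04 ≈ 93.

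93/0.90 = 103.3, rounded up to 104 per arm, 208 in total. The stated figure reproduces exactly. It is a plain two-proportion calculation that counts on no gain from stratification.

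**2. The test.** CMH statistic = (Σaₖ − ΣEₖ)² / ΣVₖ, with Eₖ = n₁ₖmₖ/nₖ and Vₖ = n₁ₖn₀ₖmₖ(nₖ−mₖ)/[nₖ²(nₖ−1)]. In stratum k, aₖ is the number of intervention successes, mₖ all successes, n₁ₖ and n₀ₖ the arm sizes and nₖ their sum. With centre as the only stratum, Vₖ still contains outcome variation due to menopausal status and modality, although allocation has balanced those factors.

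**3. Main simulation.** 186 evaluable patients (2 × 93), marginal rates 70% and 50%, 5,000 trials per setting. The following are assumptions, because the article gives no figures for them:
- the same odds ratio for each factor, from 1 to 5, with factor prevalences of 35% and 60%;
- nine uneven centres holding 3% to 35% of patients;
- between-centre log-odds SD of 0 or 0.5.

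Stratified blocks and minimisation were run separately. Ranges cover both methods and both SDs. Monte Carlo error is √(0.8·0.2/5000) ≈ 0.6 points for power and √(0.05·0.95/5000) ≈ 0.3 points for type I error.

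| Factor OR | Power, CMH by centre | Power, CMH by the two factors (4 cells) | Difference, points | Type I error, centre | Type I error, 4 cells |
|---|---|---|---|---|---|
| 1 | 78–81% | 79–80% | −0.6 to 1.5 | 0.045–0.053 | 0.045–0.051 |
| 1.5 | 79–81% | 81–82% | 0 to 2 | 0.048–0.054 | 0.048–0.054 |
| 2 | 78–81% | 81–82% | 1 to 3 | 0.043–0.051 | 0.048–0.057 |
| 3 | 80–81% | 83–84% | 3 to 5 | 0.033–0.042 | 0.044–0.056 |
| 5 | 81–82% | 88% | 6 to 7 | 0.027–0.032 | 0.047–0.053 |

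Crossing centre with both factors gives 9 × 2 × 2 = 36 cells. It yields only 73–79% power at odds ratios 1 to 3, because sparse cells carry little information.

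**4. Would replacing centre be safe?** A second simulation used 186 evaluable patients, centres of 3–30%, factors split 50/50 and 3,000 trials per scenario. It compared power as CMH by centre / CMH by four cells:

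| Factor OR | Centre SD 0.5 | Centre SD 1.0 |
|---|---|---|
| 1 | 80 / 81% | 85 / 81% |
| 1.5 | 80 / 81% | 85 / 81% |
| 2 | 80 / 82% | 84 / 81% |
| 3 | 82 / 85% | 85 / 84% |

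When centres differ strongly, dropping centre costs power.

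**5. Keeping centre and adding the factors.** With 186 evaluable patients and uneven centres, a logistic score test with centre and both factors as main effects had 81–88% power against 78–85% for centre alone, and was ahead in every scenario. Its type I error was about 5.5–6.7%, so part of that advantage comes from a slightly liberal test.

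**The case against.** **Power is as planned.** The sizing counts on no gain from stratification, and the centre-only test keeps about 80% power. What is lost is a gain the plan never claimed. This stands, and it limits the weight of the point.

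**Prognostic strength is unknown.** A reader might infer that the two factors were chosen because they predict bladder recovery, and so that power is certainly lost. The article gives neither a reason for the choice nor a strength of association. At odds ratios of 1 to 1.5 the conservatism cannot be told from simulation error. This also stands, so the point is conditional.

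**Centre adjustment is legitimate.** A reader might take adjustment for a factor outside the randomisation as an error in itself. It is not. It costs up to about 1.5 points if centres do not differ, and helps if they differ strongly. With nine hospitals, and catheter removal after day 28 timed to each patient's recovery, some difference between centres is plausible. This defeats any proposal to replace centre.

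**An article condenses the plan.** The wording does not say that centre is the only stratum, and a fuller document may list more. That is possible. But the article states the primary test twice and names its adjustment factor both times. The point concerns that stated choice, and an analysis plan that added the two factors would still call for this sentence to be aligned.

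**The allocation wording is a separate matter.** Agreed. The results were similar under either method, so the contradiction adds no weight to the analysis point.

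**Conclusion.** The point holds in a limited form. The primary test as stated adjusts for centre and omits the two factors on which allocation is balanced. If those factors are prognostic, the test is mildly conservative and forgoes about 0–2 points of power at a factor odds ratio up to 1.5, 1–3 at 2 and 3–5 at 3. These sizes rest on assumed factor strengths, factor prevalences, centre sizes and between-centre variation.

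The documents do not support reading this as an invalid or underpowered primary analysis. Type I error is not inflated, and power stays near the planned 80%. It is a cheap improvement in efficiency, worth making before the analysis is fixed.

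**What to change.** **Primary analysis.** Keep centre, and add menopausal status and surgical modality as main effects. One form is a logistic model conditional on (stratified by) centre with the two factors as covariates; another is an unconditional model with small centres pooled by a pre-stated rule. Do not cross all 36 cells, and do not replace centre with the four factor cells.

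**Cost.** One sentence in Statistical analysis and the matching one in the Abstract. Both factors are already needed for randomisation, and the sample size stays at 208. The downside is a model-based primary test in place of a simple CMH. An unconditional fit with nine centre terms runs slightly above 5% type I error, which is the reason for conditioning or pooling. Neither of those two forms was simulated here, so the error rate of the chosen one should be confirmed before it is fixed.

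**Allocation text.** Reconcile Randomisation and blinding so that it describes the one method actually used, either minimisation or stratified blocks of varying size.
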